#### *Inclusion Criteria for PLACE*

Male and female participants who meet the following eligibility criteria will be invited to participate in the project:

- At least 15 years of age at time of interview and not accompanying or running an errand for parents
- Recruited at selected venues
- Consent to participant in a face-to-face structured behavioral survey and provide written informed consent with initials or an X

Additionally participants that meet one of the following inclusion criteria for key populations will be offered additional STI testing:

- At least one sexual contact for cash in the last 12 months
- Man or transgender woman that has had oral or anal sex with another man in the past 12 months
- Identification as a male-to-female transgender woman

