### Risk assessment and collection of biologic specimens

All participants will be tested for HIV using a rapid test and finger prick at or near the recruitment venue. Based on the behavioral questionnaire described above, participants that have sold sex, identify as transgender or are men who have had sex with another man in the past 12 months will be offered additional STI testing for syphilis, Hepatitis B, gonorrhea, chlamydia and trichomoniasis. Participants that meet the definition for key population will be tested for syphilis and Hepatitis B using a rapid test and finger prick at or near the recruitment venue. Participants that test positive for syphilis with a rapid treponemal test will be offered a confirmatory test, which will be conducted at the study laboratory. Participants will be given a phone number and instructions about where and when to collect their results.

The types of tests and specimens performed on participants from the different populations are outlined in Table 1. Briefly, after consent and completion of the behavioral interview, trained counselors will provide HIV and STI pre-test counseling in a private setting. The nurse or lab technician will instruct participants how to collect vaginal swabs, urine samples and anal swabs. Among female sex workers a vaginal swab, among male key populations first-catch urine and anal swabs will be collected to test for *Neisseria gonorrhoeae*, *Chlamydia trachomatis* testing and *Trichomonas vaginalis*. Samples will be immediately stored according to the laboratory procedures manual.

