**Table 1 HIV and STI testing schematic by population approached at venues and defined in behavioral questionnaire**

| Population                | HIV rapid test | Syphilis rapid test | Hepatitis B rapid test | Vaginal swab | Urine specimen | Anal swab | CD4 rapid test | Venous blood |
|---------------------------|----------------|---------------------|------------------------|--------------|----------------|-----------|----------------|--------------|
| Female sex workers        | X              | X                   | X                      | X            |                |           |                |              |
| Male sex workers          | X              | X                   | X                      |              | X              | X         |                |              |
| Men who have sex with men | X              | X                   | X                      |              | X              | X         |                |              |
| Transgender women         | X              | X                   | X                      |              | X              | X         |                |              |
| General population        | X              |                     |                        |              |                |           |                |              |
| HIV /syphilis positive    |                |                     |                        |              |                |           | X              | X            |

The justification for the collection of anal swabs is that there have been increases in anal gonorrhea, chlamydia, including strains that cause Lymphogranuloma venereum (LGV) among men who have sex with men in various countries.

A nurse or laboratory personnel will conduct rapid HIV tests with the Determine HIV 1/2 test (Alere/Abbott Laboratories, Waltham, MA, USA) using whole blood obtained by finger prick. A negative test will be considered as a true negative, and the result will be reported to the patient after post-test counseling. A positive test will be confirmed by the Uni-gold HIV test (Trinity Biotech, Bray, Ireland). It is estimated that the HIV test results for the rapid tests will be available after 20 to 30 minutes. Results will be recorded on a HIV test results form.

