| Q12        | What is your age?                                                                                                                                                                                                                                                                                                               | IF RESPONDENT IS YOUNGER THAN 18, STOP INTERVIEW AND FIND ANOTHER. | WRITE AGE IN YEARS:                                  |  |
| Q13        | Do you work here?                                                                                                                                                                                                                                                                                                               |                                                                    | 
Yes No
 1 2                                             |  |

|     |                                                               |                    |
|-----|---------------------------------------------------------------|--------------------|
| Q14 | Were you born as a male or female?                            | MALE 1
FEMALE 2 |
| Q15 | Do you currently identify more as a male or more as a female? | MALE 1
FEMALE 2 |

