| C4  | Besides this place, how many other public places have you visited or plan to visit today to socialize, drink alcohol, or look for a person to have sex with?                                                                                                                                                                   | NUMBER:_____                                                                                                                                        |
| C5  | Have you ever had sex?                                                                                                                                                                                                                                                                                                         | 
Yes No
 
1 2
                                                                                                                            |
| C6  | Now I would like to ask about how many men and women you had sex with in the last 4 weeks, including people you had sex with once and people you had sex with more often. In total, how many men did you have sex with in the last 4 weeks?                                                                                    | MEN:_____                                                                                                                                           |
| C7  | In total, how many women did you have sex with in the last 4 weeks?                                                                                                                                                                                                                                                            | WOMEN:_____                                                                                                                                         |

|                                           |                                                                                                                                                                    |                  |         |
|-------------------------------------------|--------------------------------------------------------------------------------------------------------------------------------------------------------------------|------------------|---------|

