| C8                                        | Have you had sex with a person in the past 12 months who you never had sex with before? That is, you had sex with him or her the first time in the past 12 months. | Yes
1         | No
2 |
| C9                                        | Have you had sex with more than 10 people in the past 12 months?                                                                                                   | Yes
1         | No
2 |
| C10                                       | Have you had anal sex in the past 12 months with a man?                                                                                                            | Yes
1         | No
2 |
| C10A                                      | Did you use a condom use with your last male partner?                                                                                                              | Yes
1         | No
2 |
| NO.                                | QUESTION                                                                                                                                                    | RESPONSE  |         |
| C11                                       | Have you received money in exchange for sex in the past 12 months?                                                                                                 | Yes
1         | No
2 |
| C11A                                      | Did you use a condom use with your last client?                                                                                                                    | Yes
1         | No
2 |
| C12                                       | Have you ever received money in exchange for sex?
IF NO: GO TO C14.                                                                                             | Yes
1         | No
2 |
| C13                                       | How old were you the first time you received money in exchange for sex?
LEAVE BLANK IF NOT APPLICABLE.                                                          | WRITE AGE: _____ |         |
| C14                                       | In the last 12 months, have you given someone money to have sex?                                                                                                   | Yes
1         | No
2 |

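### The PLACE criterion for men who have sex with men covers oral or anal sex with a man in 12 months, but Form C's only 12-month item on sex with men asks about anal sex, so a narrow group of eligible men cannot be identified

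*Protocol*

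**What the plan says.** - **Criterion.** Inclusion Criteria for PLACE lists, among those offered additional STI testing, a "Man or transgender woman that has had oral or anal sex with another man in the past 12 months".
- **Testing rule.** Risk assessment and collection of biologic specimens makes the offer as follows: "Based on the behavioral questionnaire described above", "men who have had sex with another man in the past 12 months will be offered additional STI testing". The venue recruitment text in Step 4 gives the same 12-month rule and also does not restrict the sex act.
- **Population assignment.** Table 1 is titled "HIV and STI testing schematic by population approached at venues and defined in behavioral questionnaire". Its general population row carries the HIV rapid test only.
- **Instrument (Appendix 4, Form C).** C10 asks "Have you had anal sex in the past 12 months with a man". C6 asks "In total, how many men did you have sex with in the last 4 weeks" and does not define sex. C11 asks "Have you received money in exchange for sex in the past 12 months". Q15, following a question on sex at birth, asks "Do you currently identify more as a male or more as a female".
- **Gate.** The Section C header limits items C1 to C39 to respondents who are already members of a key population.
- **Condom indicator.** The Table 4 numerator is condom use at the most recent anal sex with a male partner within 12 months. C10A asks about condom use with the last male partner and names no act.

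**The concern.** The criterion and the item that should apply it share the 12-month window but not the act. Because the questionnaire decides both the population group and the STI offer, a criterion that the questionnaire cannot evaluate is not applied as written.

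Two things are at stake. First, some men who meet the protocol's own criterion would not be offered the tests planned for their group. Second, they would move from the MSM denominators to the general population, which tilts the recognised MSM sample towards men who report anal sex. The C10A mismatch is separate and wider. It touches every man who contributes to the condom indicator, because the last male partner need not be the last partner with whom he had anal sex.

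**Working it through.** The plan states no figure to reproduce. The check compares the criterion with every Form C item that could establish it.

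| Item | Window | What it covers | Can it establish the criterion? |
|---|---|---|---|
| Q14/Q15 | current | sex at birth, gender identity | only through the separate transgender route |
| C6 | 4 weeks | number of male partners, sex undefined | partly: recent contact, if the respondent counts oral sex as sex |
| C8, C9 | 12 months | new partner; more than 10 partners | no: sex of partner not asked |
| C10 | 12 months | anal sex with a man | the anal part only |
| C11 | 12 months | paid sex | only through the separate paid-sex route |

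**Who is left over.** Suppose C6 is used generously as a classifier, although no section says it is. A man is still missed when all four conditions hold:
1. his contact with men in the past 12 months was oral only;
2. he reports no male partner at C6;
3. he was not paid for sex (C11);
4. he does not identify as female (Q14/Q15).

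**The gate.** C6, C10 and C11 all lie inside Section C, which is reserved for key-population members. No earlier Form C item asks about sex with men or paid sex. Step 4 says that people approached at random are not screened on same-sex practice. If the header is applied literally, such a man is stopped before any item that could classify him. A corrected item placed inside Section C would not reach him.

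**Size.** Let f be the share of men meeting the criterion who fall in the left-over group. The documents do not give f, so these values are assumptions. Per 600 men who meet the criterion, missed = 600 × f:
- f = 2%: 600 × 0.02 = 12
- f = 5%: 600 × 0.05 = 30
- f = 10%: 600 × 0.10 = 60

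The base here is men who meet the criterion. It is not the Luanda recruitment target, which happens to be the same number.

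**Effect on an estimate, extreme case.** Assume HIV prevalence is 10% among recognised men (the Background gives an upper figure of 10.5% for Luanda) and zero in a missed group with f = 10%. The prevalence among all men meeting the criterion is then 0.90 × 10% = 9%, a shift of 1 point. The 95% half-width under simple random sampling at n = 600 is 1.96 × √(0.10 × 0.90 / 600) = 0.024, or 2.4 points, and wider if clustering inflates the variance.

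**Condom item.** The Table 4 numerator needs the most recent anal-sex occasion with a man. C10A records the most recent male partner. The two agree only when that partner was also the last anal-sex partner, and Form C holds nothing to check this.

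**The case against.** The strongest case against is that the form is provisional and other routes exist. Study Populations leaves operational definitions to the readiness assessment or to the analysis. Step 1 provides for a pilot and protocol revision, and Data Quality Control provides for replacing unclear questions at pre-test. Social mobilizers also point out key-population members at venues.

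Much of this is fair, and it lowers the severity. It does not remove the point. An analysis-stage definition cannot use an answer that was never asked for, and the specimens are collected at the venue. C10 is not unclear, only narrower than the criterion, so a pre-test for clarity may not flag it. Mobilizers may identify some of these men, but the STI offer is based on the questionnaire.

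It can also be said for C10A that its number makes it a follow-up to C10, so respondents may take it to mean anal sex. That is plausible, but the wording does not secure it.

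A reader might infer three stronger things that the documents do not support:
- **That Form C ignores all sex with men other than anal sex.** This is true only of the 12-month window. C6 covers male partners over 4 weeks, and C11 and Q14/Q15 open other routes to testing.
- **That a sizeable part of the 600 Luanda MSM, or of the 1,800 in Table 3, would be lost.** No document gives a share. Recruitment continues until the target of recognised participants is reached, so missed men are additional to the 600 and not subtracted from them. Extending STI losses to all provinces is also uncertain. The Background places the HIV/STI biomarkers in Luanda, although Table 3 heads its rows in every province as interview and testing.
- **That prevalence estimates are seriously biased.** Even the extreme case above moves the estimate by less than its sampling error.

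**Conclusion.** The mismatch is confirmed on the text: the PLACE criterion cannot be applied from Form C as written. The men affected had oral-only contact, report no male partner in 4 weeks, were not paid for sex and do not identify as female. Their number is unknown and probably small. The 12 to 60 per 600 rests entirely on an assumed 2% to 10%. The direction is clear, since the recognised MSM sample leans towards anal sex, but a material shift in prevalence is not shown. The C10A mismatch with Table 4 stands at any share. Severity is minor to moderate: few men are likely to be affected, but the loss cannot be repaired after fieldwork.

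**What to change.** If the PLACE criterion stands:
1. Add an item on oral or anal sex with a man in the past 12 months. Place it before the Section C gate and name it as the classification item.
2. Keep anal sex with a man in the past 12 months as a separate follow-up.
3. Reword C10A to condom use the last time the respondent had anal sex with a man.

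The gate itself should rest on items already asked, so the paid-sex item (C11) belongs before it as well.

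If the investigators instead intend the narrower definition, Inclusion Criteria for PLACE, the Step 4 testing text and the specimen section should be reconciled with C10. Which definition governs the testing offer is for them to decide. What matters here is that the criterion and the instrument agree.

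The cost is one added question, one rewording and one item moved in Form C, which the planned pilot and revision can absorb before fieldwork.

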**Table 4 Key indicators targeting MSM used by FHI, UNAIDS, and PEPFAR for behavioral surveillance purposes.**

| Cascade Step      | Indicator                                                                                                                                   | Indicator # | Measure                                                                                                                                                    |
|--------------------------|----------------------------------------------------------------------------------------------------------------------------------------------------|--------------------|-------------------------------------------------------------------------------------------------------------------------------------------------------------------|
| Identify population size | Estimated total number of key populations in the program geographic area (denominator for KP_PREV)                                                 | PMP 1.1b (denom.)  |                                                                                                                                                                   |
| Reach people, Coverage   | Percentage of people from key population who have received free condoms and lubricant in the past 12 months                                        | WHO CCP-3, CCP-5   | Num: Number of respondents who received free condoms and lubricant in the past 12 months

Denom: Number of people interviewed                               |
|                          | Percentage of respondents who have been tested for HIV during the last 12 months and who know their results (prior to participation in the survey) | GARPR 1.9 & 1.13   | Numerator: Number of respondents who have been tested for HIV during the last 12 months and who know the results.

Denominator: Total number of respondents |

Programmatic Mapping and HIV/STI Prevalence Study among Key Populations in Angola

| Cascade Step | Indicator                                                                                                                                                                                                   | Indicator #          | Measure                                                                                                                                                                                                                                         |

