|--------------|-------------------------------------------------------------------------------------------------------------------------------------------------------------------------------------------------------------|----------------------|-------------------------------------------------------------------------------------------------------------------------------------------------------------------------------------------------------------------------------------------------|
|              | Percentage of people from key population who have been screened for STI in the past 12 months (prior to participation in the survey)                                                                        | WHO SRH-4            | Num: Number of respondents who have been screened for STI in the past 12 months

Denom: Number of people interviewed                                                                                                                      |
|              | Percentage of people from key population who have received information on HIV, AIDS, condoms or safe sex in the past 12 months (from an outreach or health worker)?                                         |                      | Num: Number of respondents who have received information on HIV, AIDS, condoms or safe sex in the past 12 months?

Denom: Number of people interviewed                                                                                    |
|              | Key population reporting they have received a combined set of health sector interventions                                                                                                                   | WHO PKG-2            | Condoms; lubricant; information on condom use and safe sex; HTC; STI screening;                                                                                                                                                                 |
|              | Proportion of key populations reached with individual and/or small group level HIV preventive interventions that are based on evidence and/or meet the minimum standard required (KP_PREV/CUSTOM INDICATOR) | PMP 1.1b             | Num: Number of respondents who have received any of the above interventions in the past 12 months

Denom: Number of people interviewed                                                                                                    |

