|              | Percentage of people from key population reached with HIV prevention programs                                                                                                                               | GARPR 1.7, 1.11, 2.1 | Participants who respond, 'Yes' to the following questions:

1. Do you know where you can go if you wish to receive an HIV test?

2. In the last 12 months, have you been given condoms?

Denom: Number of people interviewed |
| Test people  | Proportion of key populations who received HIV testing and counseling services for HIV and received their test results (HTC-3, GARPR 1.9, 1.13 & 2.4)                                                       | 1.3b                 | Num: Number of people tested for HIV who receive their results

Denom: Estimated number of key population living with HIV in the program geographic area                                                                                  |

Programmatic Mapping and HIV/STI Prevalence Study among Key Populations in Angola

| Cascade Step         | Indicator                                                                | Indicator #            | Measure                                                                                                                      |
|----------------------|--------------------------------------------------------------------------|------------------------|------------------------------------------------------------------------------------------------------------------------------|
| Prevalence           | Percentage of people from key population who are living with HIV         | GARPR 1.10, 1.14 & 2.5 | Num: Number of people diagnosed with HIV
Denom: Number of people tested for HIV                                           |
|                      | Percentage of people from a key population diagnosed syphilis            | WHO O-3b               | Num: Number of people diagnosed with active syphilis
Denom: Number of people tested for syphilis                          |
|                      | Percentage of people from a key population diagnosed gonorrhea           | WHO O-3b               | Num: Number of people diagnosed with gonorrhea
Denom: Number of people tested for gonorrhea                               |

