| QUESTIONS ABOUT ACCESS TO SERVICES |                                                                                                                                                                    |                  |         |
| C15                                       | If you wanted a condom, would it be easy to get one?                                                                                                               | Yes
1         | No
2 |
| C16                                       | In the past 12 months, has an outreach worker such as a peer educator given you a condom?                                                                          | Yes              | No      |

|            |                                                                                                                                                               |                                                                                   |
|------------|---------------------------------------------------------------------------------------------------------------------------------------------------------------|-----------------------------------------------------------------------------------|
|            |                                                                                                                                                               | 1 2                                                                               |
| C17        | Do you have a condom with you now?                                                                                                                            | Yes No
1 2                                                                     |
| C18A       | In the last 12 months, have you had any burning when you pee, or discharge from your penis or vagina or anus, or sores on your genitals?                      | Yes No
1 2                                                                     |
| C18B       | IF YES: In the last 12 months, have you sought care for any of these symptoms at a public or private clinic?
IF NOT APPLICABLE (C18=2) THEN CIRCLE 9 (NA). | Yes No NA
1 2 9                                                                |

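### Form C item C16 records only condoms given by an outreach worker, while the Table 4 condom components set no source limit, so the condom component is biased downward by an unknown amount

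*Protocol*

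**What the plan says.** **Form C (Appendix 4).** C16 asks "In the past 12 months, has an outreach worker such as a peer educator given you a condom". The neighbouring condom items measure other things: C15, "If you wanted a condom, would it be easy to get one", is about access, and C17, "Do you have a condom with you now", is about possession. C10A and C11A concern condom use. No other Form C item asks about having been given condoms.

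**Table 4 (Protocol, section VIII.B).** Condom receipt enters four rows:

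- WHO CCP-3/CCP-5: "Percentage of people from key population who have received free condoms and lubricant in the past 12 months", with the numerator "Num: Number of respondents who received free condoms and lubricant in the past 12 months".
- WHO PKG-2, the combined set, which lists condoms and lubricant as separate components beside safe-sex information, HIV testing and counselling, and STI screening.
- PMP 1.1b, whose numerator counts anyone who had at least one of the interventions listed above it.
- GARPR 1.7/1.11/2.1, which needs a yes to two questions: "Do you know where you can go if you wish to receive an HIV test" and "In the last 12 months, have you been given condoms".

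None of these names a giver. The row on HIV information does name one: "from an outreach or health worker".

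**The concern.** The form measures a narrower event than the indicators it is meant to feed. Table 4 states a source where one is intended, so its silence in the condom rows cannot easily be read as meaning outreach only. Form C draws the same distinction for information: C21 asks about an outreach worker at the site and C23 about any health worker. For condoms there is an outreach item and no health-worker counterpart.

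Section V makes finding gaps in condom and other prevention services an objective, and section VIII.B names condom distribution among the coverage indicators. An area where condoms come mainly from clinics could look less served than it is. PLACE is cross-sectional and the interview collects no identifying information, so the missing answer could not be obtained afterwards. A larger sample or weighting would not correct a question that was never asked.

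**Working it through.** There is no figure in the Protocol to reproduce. The check compares the item with the indicators, then bounds the effect under assumptions.

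**Step 1: direction for the condom component.** Let A be given condoms by an outreach worker (C16) and B be given condoms, source unspecified (Table 4). Everyone in A is in B, but not the reverse. The denominator, people interviewed, is the same. Using A for B can therefore only lower the proportion or leave it unchanged.

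**Step 2: size.** Two inputs are needed and the documents give neither, so both are assumed:

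- p = true proportion given condoms in the past 12 months
- s = share of those recipients for whom an outreach worker was a source

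C16 result = p × s. Shortfall = p × (1 − s).

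| p | s = 0.9 | s = 0.7 | s = 0.5 | s = 0.3 |
|---|---|---|---|---|
| 30% | 27% (−3) | 21% (−9) | 15% (−15) | 9% (−21) |
| 50% | 45% (−5) | 35% (−15) | 25% (−25) | 15% (−35) |
| 70% | 63% (−7) | 49% (−21) | 35% (−35) | 21% (−49) |

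Cells give the C16 result and, in brackets, the shortfall in points. At s = 1 the shortfall is zero. With n = 600 (the Luanda target for sex workers and for MSM, section VI.E), p = 50% and s = 0.7, the number misclassified is 600 × 0.5 × 0.3 = 90.

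For scale, the 95% half-width at n = 600 is 1.96 × √(DEFF × p(1 − p)/600). At p = 50% this is 4.0 points for DEFF 1 and 5.7 for an assumed DEFF of 2. At p = 30% or 70% it is 3.7 and 5.2.

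**Step 3: PMP 1.1b.** Take condoms as an intervention in their own right, as the PKG-2 list does. If u is the share of the misclassified people whom Form C still captures through another counted intervention, such as information from a health worker (C23) or a recent HIV test with result (C29 and C30), the loss in this row is p × (1 − s) × (1 − u). Only people whose sole intervention was a non-outreach condom drop out.

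**Step 4: multi-part rows.** CCP-3/5 also needs lubricant, PKG-2 also needs lubricant and STI screening, and GARPR 1.7/1.11 also needs knowledge of a test site. Form C has no item for any of these; C18A and C18B cover symptoms and care-seeking, not screening. The rows cannot be computed as defined. Suppose C16 alone stood in for a two-part row, and a share q of condom recipients also met the second condition. C16 gives p × s; the definition gives p × q. With p = 50% and s = 0.7:

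- q = 0.20: C16 gives 35%, the definition 10%; error +25 points.
- q = 0.95: C16 gives 35%, the definition 47.5%; error −12.5 points.

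The sign depends on whether s exceeds q, so no net direction follows.

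**The case against.** A reader might infer that prevention coverage as a whole is understated in all four rows. The documents do not support that. Three of the rows lack a required component in Form C and, by step 4, could come out too high if C16 stood in alone. In PMP 1.1b the downward effect is real but diluted.

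A reader might also infer that anyone given condoms by an NGO or at a venue must answer no to C16. That goes too far. The peer educator in C16 is only an example, so NGO outreach staff fit the wording. Form B item B22 records free condom distribution at a venue without saying who carried it out; outreach workers may do it, and the answer is then yes. C18D does not show other condom channels either, because it asks where care was sought and follows the STI-symptom items. The clear case is a non-outreach source such as clinic staff.

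Three further points are fair. The size is wholly assumed, and would be nil if outreach reached every recipient. Table 4 is used for the Cabinda RDS survey as well, whose questionnaire (Appendix 5) is not in the text at hand, so the point is confined to PLACE. Step 1 of the PLACE procedures plans a pilot with revision, and section VII.E plans replacement of unclear questions at pre-test. C16, however, is clear as it stands; it asks about a narrower event than Table 4 defines, and nothing commits the team to change it.

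**Conclusion.** The point holds for the PLACE survey, limited to the condom component. C16 is the only receipt item, it names the giver, and Table 4 does not. People given condoms only by non-outreach sources are counted as not having received them, so the condom component is biased downward or, at best, unaffected.

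The amount cannot be derived from the documents. The 3 to 49 point range rests entirely on the assumed p of 30% to 70% and s of 0.3 to 0.9. It shows that the error could exceed sampling error, not that it will. For PMP 1.1b the direction holds with other things equal, at a smaller size. For CCP-3/5, PKG-2 and GARPR 1.7/1.11 no net direction is established, because the rows cannot be computed from Form C at all.

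**What to change.** Before PLACE fieldwork:

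1. Reword C16 to: *In the past 12 months, have you been given free condoms?* Add a sub-item on source (outreach worker, health facility, venue, other; all that apply), which keeps the outreach-only figure.
2. Use the unrestricted answer for the condom component of CCP-3/5, PKG-2, PMP 1.1b and GARPR 1.7/1.11.
3. Rewording C16 does not by itself make CCP-3/5, PKG-2 or GARPR 1.7/1.11 computable. Add short items on receipt of free lubricant, STI screening in the past 12 months, and knowing where to get an HIV test. Otherwise, redefine those Table 4 rows as what Form C measures and label the condom figure as outreach-delivered.

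The cost is one reworded item, one sub-item and up to three short additional items: a few extra seconds per interview, with matching changes to the smartphone form and its translations.
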